# The Effect of Plasma Triglyceride-Lowering Therapy on the Evolution of Organ Function in Early Hypertriglyceridemia-Induced Acute Pancreatitis Patients With Worrisome Features (PERFORM Study): Rationale and Design of a Multicenter, Prospective, Observational, Cohort Study

**DOI:** 10.3389/fmed.2021.756337

**Published:** 2021-12-13

**Keywords:** acute pancreatitis (AP), hypertriglyceridemia (HTG), TG-lowering therapy, organ failure free day, cohort study

## Abstract

**Background:** Acute pancreatitis (AP) is a potentially life-threatening inflammatory disease with multiple etiologies. The prevalence of hypertriglyceridemia-induced acute pancreatitis (HTG-AP) has been increasing in recent years. It is reported that early triglyceride (TG) levels were associated with the severity of the disease, and TG- lowering therapies, including medical treatment and blood purification, may impact the clinical outcomes. However, there is no consensus regarding the optimal TG-lowering therapy, and clinical practice varies greatly among different centers. Our objective is to evaluate the TG-lowering effects of different therapies and their impact on clinical outcomes in HTG-AP patients with worrisome features.

**Methods:** This is a multicenter, observational, prospective cohort study. A total of approximately 300 patients with HTG-AP with worrisome features are planned to be enrolled. The primary objective of the study is to evaluate the relationship between TG decline and the evolution of organ failure, and patients will be dichotomized depending on the rate of TG decline. The primary outcome is organ failure (OF) free days to 14 days after enrollment. Secondary outcomes include new-onset organ failure, new-onset multiple-organ failure (MOF), new-onset persistent organ failure (POF), new receipt of organ support, requirement of ICU admission, ICU free days to day 14, hospital free days to day 14, 60-day mortality, AP severity grade (Based on the Revised Atlanta Classification), and incidence of systemic and local complications. Generalized linear model (GLM), Fine and Gray competing risk regression, and propensity score matching will be used for statistical analysis.

**Discussion:** Results of this study will reveal the current practice of TG-lowering therapy in HTG-AP and provide necessary data for future trials.

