For the target of TG-lowering therapy, it is regarded that reducing the TG level to 5.65 mmol/L might be clinically sufficient (20). Lu et al. (10) found that patients with earlier TG levels of < 5.65 mmol/L were less likely to develop POF. However, the optimal TG lowering target and choice of therapies in early HTG-AP are unclear due to the lack of high-quality studies. Given the paucity of evidence in the literature and the variation in the management of HTG-AP, we conducted this multicenter, observational study and built “The effect of plasma triglyceride-lowering therapy on the evolution of organ function in early hypertriglyceridemia-induced acute pancreatitis patients with worrisome features”(PERFORM) registry to evaluate the TG-lowering effects of different therapies and their impact on clinical outcomes in HTG-AP patients with worrisome features.

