## Methods

### Study Objectives

The primary objective of the study is to evaluate the relationship between TG decline and the evolution of organ failure in a cohort of early HTG-AP patients with worrisome features. The secondary objectives are to characterize the current clinical practice regarding TG-lowering therapy, describe the association between different choices of therapy and clinical outcomes. The third objective is to provide data for future trials. Accordingly, every secondary endpoint is also supposed to be hypothesis generating.

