### Inclusion Criteria

1. Age Between 18 and 70 Years old;2. Within 72 H From the Onset of Abdominal Pain;3. Symptoms and Signs of AP Based on Abdominal Pain Suggestive of AP, Serum Amylase at Least three Times the Upper Limit of Normal, and/or Characteristic Findings of AP on Computed Tomography or Less Commonly Magnetic Resonance Imaging (MRI) or Transabdominal Ultrasonography According to the Revised Atlanta Criteria (21).4. When Enrolled, TG > 1,000 mg/dL (11.3 mmol/L), Accompanied by the Clinical Features of any one or More of the Following (22):1) Signs of hypocalcemia (calcium levels < 2 mmol/L);2) Lactic acidosis (Lactate levels more than 2 mmol/L and PH < 7.35);3) The systemic inflammatory response syndrome (SIRS) is clinically recognized by the presence of two or more of the following:a) Temperature >38.5°C or <35.0°C;b) Heart rate of >90 beats /min;c) Respiratory rate of >20 breaths/min or PaCO2 of <32 mmHg;d) WBC count of >12, 000 cells/mL, <4,000 cells/mL, or >10 percent immature (band) forms;4) Organ failure defined by the sequential organ failure assessment (SOFA) score for respiration, renal and cardiovascular systems.

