### Statistical Analysis

Continuous normally distributed data were reported as means with SDs. Skewed continuous data were reported as medians and interquartile ranges (IQRs). Categorical data will be summarized by counts and percentages. The intergroup difference will be compared by Student's *t*-test or Wilcoxon rank-sum test for continuous variable depending on their normality and chi-square test for categorical data.

To evaluate the association between TG decline and OF free days, the study patients will be dichotomized depending on whether the TG level reaches 5.65 mmol/L on Day 3 (the day of enrollment is labeled Day 1, the next day labeled Day 2, and the following day Day 3). For the primary outcome comparison, Wilcoxon rank-sum test will be employed. However, since OF could be evaluated with a time-to-event analysis censored at 14 days to account for the mortality as a competing event, Fine and Gray competing risk regression is used to assess the group difference as a supportive analysis.

For the association between different TG lowering therapy and OF free days, we considered the possibility that baseline characteristics, which were expected to be prognostic for OF, differ according to the choice of TG lowering therapies (i.e., blood purification treatment and medical treatment). A propensity score matching will be further used to compensate for the intergroup unbalance.

For secondary outcomes, a multivariate analysis generalized linear model (GLM) model will be performed to identify its association with TG decline and TG-lowering therapy with proper link and distribution function. The variable included in the model will be age, sex, TG level at enrollment, and other baseline variables that have significant differences between groups.

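### Primary exposure is described as TG decline but analysed as reaching 5.65 mmol/L on Day 3; group membership then depends partly on enrollment TG, which the primary test leaves unadjusted

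*Protocol article*

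**What the plan says.** The Abstract names the exposure as a rate: "patients will be dichotomized depending on the rate of TG decline". Study Objectives states the primary aim as to "evaluate the relationship between TG decline and the evolution of organ failure".

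The Statistical Analysis section defines the groups differently. Patients are "dichotomized depending on whether the TG level reaches 5.65 mmol/L on Day 3", which is an absolute level at one time. The Sample Size Justification uses the same contrast, target TG achieved or not. The Background gives the reason for the cut-point: "it is regarded that reducing the TG level to 5.65 mmol/L might be clinically sufficient".

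The Inclusion Criteria require TG above 11.3 mmol/L at enrollment and set no upper limit.

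On the test, the Statistical Analysis section says: "For the primary outcome comparison, Wilcoxon rank-sum test will be employed". Fine and Gray regression is the supportive analysis, and no covariates are named for it. Propensity score matching is planned for the comparison of therapies. TG at enrollment is listed as a covariate, with age and sex, in the generalized linear model (GLM) for secondary outcomes.

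**The concern.** A level on a given day and a decline up to that day are different quantities unless everyone starts from the same value. Here they do not. Two patients with the same proportional fall can land in different groups only because one entered with a higher TG.

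That matters because the article treats TG level as prognostic. The Background cites a study in which higher serum TG went with more persistent organ failure, and the Discussion says that several studies associate TG level with organ failure. If this holds within the enrolled range, patients with high entry TG are both less likely to reach 5.65 mmol/L and more likely to have organ failure. An unadjusted comparison could then favour the patients who reach the target even if the speed of decline had no effect. The finding would be read as support for lowering TG quickly when part of it was a difference in starting level.

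**Working it through.** **Inputs.** Cut-point 5.65 mmol/L on Day 3 (Statistical Analysis). Entry TG above 11.3 mmol/L (Inclusion Criteria). A 69.6% fall after plasmapheresis (Discussion). 240 evaluable patients, and differences of 2 days (SD 5) or 1.5 days (SD 4) (Sample Size Justification).

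**1. The plan's own figure.** Assume 120 patients per group and two-sided alpha 0.05; the article states neither. Power = Φ(d·√(120/2) − 1.96).
- 2 days, SD 5: d = 0.40; 0.40 × 7.746 − 1.96 = 1.138; power 87.3% (87.0% with the t distribution; stated 87%).
- 1.5 days, SD 4: d = 0.375; 0.375 × 7.746 − 1.96 = 0.945; power 82.8% (82.5% with the t distribution; stated 82.5%).

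The stated power reproduces for the two-group contrast and is not in question.

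**2. Fall needed to reach the target.** Required fall = 1 − 5.65/E, where E is enrollment TG. Only 11.3 comes from the article; the other values of E are illustrative.

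| E (mmol/L) | 5.65/E | Required fall |
|---|---|---|
| 11.3 | 0.500 | 50% |
| 15 | 0.377 | 62% |
| 20 | 0.283 | 72% |
| 30 | 0.188 | 81% |
| 40 | 0.141 | 86% |

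**3. Same decline, different group.** With a fall of 69.6%, Day 3 TG is 0.304 × E. This is at or below 5.65 only if E ≤ 5.65/0.304 = 18.6 mmol/L. Patients entering above that count as not reaching the target, although their proportional decline is the same.

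**4. Larger decline, worse label.** A fall from 40 to 8 mmol/L is 80% and misses the target. A 51% fall from 11.4 gives 11.4 × 0.49 = 5.59 mmol/L and meets it.

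**5. What adjustment does.** Among patients with the same E, reaching 5.65 is exactly the same as falling by at least 1 − 5.65/E, so within a given enrollment TG the split is a split on decline. The continuous version shows the same: β·log(D3/E) + γ·log E = β·log D3 + (γ − β)·log E. Once log E is in the model, the coefficient β is identical for level and for decline. The gap between the stated and the analysed exposure therefore matters mainly because the primary test leaves E out.

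**The case against.** The strongest reply is that the body of the article is consistent. Background, Sample Size Justification, Statistical Analysis and Discussion all work with the 5.65 mmol/L target, and the Statistical Analysis section presents the split as its way of studying TG decline. Everyone enters above 11.3 mmol/L, so reaching 5.65 by a fixed day always means a fall of at least 50% and is a coarse measure of speed. On this view, the Abstract's rate is loose wording rather than a second planned analysis. Much of this stands. It supports keeping target attainment as the exposure and correcting the Abstract. It does not answer the confounding, because the minimum fall still rises from 50% to 86% between entry values of 11.3 and 40 mmol/L.

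A second reply is that covariates may be set out in an analysis plan that is not shown. That could be so for the Fine and Gray model. It does not rescue the primary comparison, which the article fixes as a rank-sum test with no place for a covariate.

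A reader might go further and infer that the split largely re-labels baseline TG. The article gives no distribution of enrollment TG or of decline, so the share of group membership that is due to baseline cannot be determined. It could be minor or dominant.

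A reader might also infer that dichotomising throws away more than a third of the information. That figure requires a normally distributed exposure with a linear effect. The article's hypothesis is a clinical target, and under a true threshold effect the figure does not apply. The planned power was in any case calculated for the two-group contrast.

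**Conclusion.** The point holds in a limited form. The Abstract and objective describe decline, whereas the primary analysis uses attainment of an absolute level. Because the required fall depends on enrollment TG, the groups will partly differ in enrollment TG, and the primary comparison does not account for it. The article already treats enrollment TG as worth adjusting for in the secondary-outcome GLM, so leaving it out of the primary comparison is hard to justify.

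The dependence of the required fall on entry TG is arithmetic and needs no assumption. That this biases the primary result rests on two assumptions: that enrollment TG varies materially above 11.3 mmol/L, and that it predicts organ failure within that range, as the cited evidence suggests. The direction would then favour patients who reach the target. The size cannot be derived from the article. The case for change is nevertheless sound, because the correction uses a value that every eligible patient must have.

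**What to change.** - Keep reaching 5.65 mmol/L on Day 3 as the primary exposure.
- Base the primary comparison of organ-failure-free days on a model adjusted for log enrollment TG. A proportional-odds model is the natural adjusted analogue of the Wilcoxon test and suits an outcome in days with a cluster at zero. Name log enrollment TG as a covariate in the supportive Fine and Gray model too.
- Pre-specify a sensitivity analysis with continuous log(Day 3 TG / enrollment TG), adjusted for log enrollment TG.
- Reword the Abstract and primary objective to target attainment by Day 3. At the same time, settle which day is meant: the Statistical Analysis section calls the enrollment day Day 1, and Table 1 calls it Day 0.

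No new data are needed, since enrollment TG is required for eligibility and TG is among the daily laboratory tests. The cost is slightly more analysis and a primary result that depends on a model, including its proportional-odds assumption, rather than on a rank-sum test. The unadjusted Wilcoxon result can be reported beside it. The change should be dated and made before the outcome data are analysed. Making continuous decline the primary exposure would be a larger step, because it would replace the contrast on which the sample size rests; the article does not compel it.

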## Background

Acute pancreatitis (AP) is a potentially life-threatening inflammatory disease caused by multiple etiologies, such as alcohol, gallstones, and hypertriglyceridemia (HTG). HTG is the third most common cause of AP, accounting for 4–10% of cases globally, and the increasing prevalence of HTG-AP had been reported in recent studies (1–4). In China, HTG had been the second leading cause of AP, and previous studies showed that HTG-AP patients had a higher risk of severe acute pancreatitis and multiple organ dysfunction syndrome (MODS) than other types of AP (2, 5–7).

Although the pathophysiology underlying HTG-AP remains controversial, it is widely accepted that free fatty acid (FFA) is one of the driving factors (8). FFA, produced by the hydrolysis of triglyceride (TG), can initiate or worsen the disease by triggering inflammatory reactions, damaging the pancreatic cell, and promoting microvascular thrombosis within the pancreatic tissue (9). Nawaz et al. (6) found that elevated serum TG levels in AP patients were independently and proportionally correlated with persistent organ failure (POF) regardless of etiology. In an observational study conducted by Lu et al. (10) timely reduction of serum TG during the early phase of HTG-AP was found to be associated with decreased incidence of POF.

Over the past years, several attempts had been made to lower serum TG more efficiently during the acute phase of the disease, including medical treatment with insulin and/or heparin, blood purification, and gene therapy in cases (11). Medical treatment is convenient and safe and is considered the first-line choice for TG-lowering therapy (4). Heparin stimulates the release of endothelial lipoprotein lipase into circulation, while insulin activates lipoprotein lipase, thereby increasing the clearance of chylomicrons from plasma (12). However, the impact of medical therapy on clinical outcomes is uncertain, and an observational study is ongoing to figure it out (13). Blood purification, especially plasmapheresis, is also widely used in TG-lowering therapy. Plasmapheresis rapidly removes triglycerides from plasma and is considered one of the most efficient TG-lowering therapies (14). Technically, it is a therapeutic procedure in which the blood of the patient is passed through a medical device that separates plasma from other components of blood. The plasma is removed and replaced by a replacement solution (e.g., albumin and/or plasma) or a combination of crystalloid/colloid solution (15). Double filtration plasmapheresis (DFPP) is a semi-selective apheresis method based on a double filter system, which can remove macromolecules selectively (16). Both techniques are widely adopted, while plasmapheresis is thought to be more effective in removing FFA (17). Other blood purification modalities were also reported effective in lowering plasma TG, including hemoperfusion and hemofiltration (18, 19). A randomized control trial (RCT) reported that high-volume hemofiltration (HVHF) decreased TG levels more efficiently than medical therapy (18).

For the target of TG-lowering therapy, it is regarded that reducing the TG level to 5.65 mmol/L might be clinically sufficient (20). Lu et al. (10) found that patients with earlier TG levels of < 5.65 mmol/L were less likely to develop POF. However, the optimal TG lowering target and choice of therapies in early HTG-AP are unclear due to the lack of high-quality studies. Given the paucity of evidence in the literature and the variation in the management of HTG-AP, we conducted this multicenter, observational study and built “The effect of plasma triglyceride-lowering therapy on the evolution of organ function in early hypertriglyceridemia-induced acute pancreatitis patients with worrisome features”(PERFORM) registry to evaluate the TG-lowering effects of different therapies and their impact on clinical outcomes in HTG-AP patients with worrisome features.

## Methods

### Study Objectives

The primary objective of the study is to evaluate the relationship between TG decline and the evolution of organ failure in a cohort of early HTG-AP patients with worrisome features. The secondary objectives are to characterize the current clinical practice regarding TG-lowering therapy, describe the association between different choices of therapy and clinical outcomes. The third objective is to provide data for future trials. Accordingly, every secondary endpoint is also supposed to be hypothesis generating.

### Study Design

The PERFORM study is a multicenter, observational, prospective cohort study. The overall cohort is HTG-AP patients presenting with worrisome features. It was registered on October 30th, 2020, in the Chinese Clinical Trial Registry (ChiCTR2000039541, https://www.chictr.org.cn/index.aspx). The PERFORM study was designed and coordinated by the Chinese Acute Pancreatitis Clinical Trials Group (CAPCTG).

### Study Population

Recruitment started on November 1st, 2020, and is scheduled to end on October 31st, 2022. This study is planned to recruit patients admitted to 30–40 hospitals across China. All adult patients presenting with early HTG-AP with worrisome features would be consecutively enrolled. The definition for HTG-AP with worrisome features is indicated as below.

All adult patients with AP admitted to the participating centers will be assessed for eligibility after admission (Figure 1). The inclusion and exclusion criteria are as follows:

**Figure 1 F1:**
[figure not shown]
Flow chart of participants.

### Inclusion Criteria

1. Age Between 18 and 70 Years old;2. Within 72 H From the Onset of Abdominal Pain;3. Symptoms and Signs of AP Based on Abdominal Pain Suggestive of AP, Serum Amylase at Least three Times the Upper Limit of Normal, and/or Characteristic Findings of AP on Computed Tomography or Less Commonly Magnetic Resonance Imaging (MRI) or Transabdominal Ultrasonography According to the Revised Atlanta Criteria (21).4. When Enrolled, TG > 1,000 mg/dL (11.3 mmol/L), Accompanied by the Clinical Features of any one or More of the Following (22):1) Signs of hypocalcemia (calcium levels < 2 mmol/L);2) Lactic acidosis (Lactate levels more than 2 mmol/L and PH < 7.35);3) The systemic inflammatory response syndrome (SIRS) is clinically recognized by the presence of two or more of the following:a) Temperature >38.5°C or <35.0°C;b) Heart rate of >90 beats /min;c) Respiratory rate of >20 breaths/min or PaCO2 of <32 mmHg;d) WBC count of >12, 000 cells/mL, <4,000 cells/mL, or >10 percent immature (band) forms;4) Organ failure defined by the sequential organ failure assessment (SOFA) score for respiration, renal and cardiovascular systems.

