### Primary Outcome Measure

The primary outcome is organ failure (OF) free days to 14 days after enrollment. Only the final period of OF-free days is included, and patients who have OF at day 14 or died before day 14 are assigned to zero OF-free days.

Secondary outcome measures

Part I: Secondary outcomes during the index admission

New-onset organ failure;New-onset multiple-organ failure (MOF);New-onset persistent organ failure (POF);New receipt of organ support;Requirement of ICU admission;ICU free days to day 14;Hospital free days to day 14;

Part II: Secondary outcomes within 60 days after enrollment

Mortality censored at 60 days after enrollment;AP severity grade (Based on the Revised Atlanta Classification);Incidence of infected pancreatic necrosis (IPN);Incidence of septic shock;Incidence of abdominal bleeding;Incidence of gastrointestinal fistula.

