### Definition of Outcomes

An individual SOFA score of 2 or more for the respiration, cardiovascular, or renal system is defined as the presence of organ failure. New-onset organ failure is defined as organ failure that is not present at any time in the 24 h after enrollment. Multiple organ failure is defined as two or more organ failures present at the same time. Persistent organ failure is defined as organ failure that persists for more than 48 h. ICU free days to day 14 after enrollment is defined as the number of days alive and not admitted to an ICU after the patient's latest discharge from the ICU before day 14. If the patient is admitted to an ICU on day 14 or dies prior to day 14, ICU-free days will be 0. Hospital-free days to day 14 after enrollment is defined as the number of days alive and not admitted to the hospital after the patient's final discharge from the hospital before day 14.

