### Data Collection and Management

A web-based electronic database (access through the website of the CAPCTG, https://capctg.medbit.cn/) is used for data collection and storage. All data are de-identified and input by the primary investigator or nominated investigators (less than two for each participating center) approved by the primary investigator, and a double check will be done by the research coordinator. Training for data entry is performed by the provider of the electrical database (Unimed Scientific, Inc, Wuxi, China) and the coordinating and data management center of the CAPCTG. Data including demographic characteristics, baseline characteristics, daily laboratory test, daily TG-lowering treatment, daily SOFA score, and follow-up characteristics. Demographic characteristics include age and sex. Baseline characteristics include body mass index (BMI), SOFA score on admission, Acute Physiology and Chronic Health Evaluation II (APACHE II) score on admission, the systemic inflammatory response syndrome (SIRS) on admission. Daily laboratory tests include serum total cholesterol (TC), triglyceride (TG), high-density lipoprotein cholesterol (HDL-c), low-density lipoprotein cholesterol (LDL-c), apolipoprotein A1 (Apo A1), apolipoprotein B (Apo B), apolipoprotein E (Apo E), lipoprotein a [LP(a)], free fatty acids (FFA), C-reactive protein (CRP), and procalcitonin (PCT). Daily TG-lowering treatment includes blood purification treatment (e.g., plasma exchange, hemoperfusion, and hemofiltration) and medical treatment (e.g., insulin and heparin). Follow-up characteristics include ICU days, hospital days, in-hospital cost, revision of the Atlanta classification on admission, CT severity index (CTSI) score (Based on the last image before discharge or death), mortality, and incidence of major complications on day 60. According to the schedule shown in Table 1, the investigators are required to collect data during the index admission and on day 60 after enrollment. And a follow-up on day 60 will be implemented through telephone.

**Table 1 T1:** Schedule of enrollment, assessment and follow up.

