**Follow up:**				
Vital status				X
Major complication				X
ICU days and hospital days				X
Cost				X

a *Day0 is defined as the day from enrollment to 8 am the next day*.

b *DayX is defined as the day from 8 am day X after enrollment to 8 am the next day*.

: *Assessments during this period need to be repeated on a daily basis*.

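### Patients may enter at any time up to 72 h after pain onset, yet the primary comparison ignores time since onset, so disease stage at entry can confound the TG-target contrast

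*Protocol article*

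**What the plan says.** All references are to the protocol article.

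- **Entry window (Inclusion Criteria).** "Within 72 H From the Onset of Abdominal Pain".
- **TG criterion (Inclusion Criteria).** "When Enrolled, TG > 1,000 mg/dL (11.3 mmol/L), Accompanied by the Clinical Features of any one or More of the Following". The level is required at enrolment, not at onset or at its peak.
- **Exposure (Statistical Analysis).** Patients are "dichotomized depending on whether the TG level reaches 5.65 mmol/L on Day 3", with this numbering: "the day of enrollment is labeled Day 1, the next day labeled Day 2, and the following day Day 3".
- **Primary outcome (Primary Outcome Measure).** "The primary outcome is organ failure (OF) free days to 14 days after enrollment". Only the last failure-free stretch counts; organ failure at day 14, or death before it, scores zero.
- **New-onset failure (Definition of Outcomes).** "New-onset organ failure is defined as organ failure that is not present at any time in the 24 h after enrollment".
- **Analysis (Statistical Analysis).** The primary comparison is a Wilcoxon rank-sum test, supported by a Fine and Gray model of the group difference; no covariate is named for either. The generalized linear models (GLMs) for secondary outcomes take age, sex, enrolment TG and any baseline variable that differs significantly between groups. Propensity matching is described only for the comparison of therapies, and its variables are not listed.
- **Baseline data (Data Collection and Management).** "Baseline characteristics include body mass index (BMI), SOFA score on admission", followed by APACHE II and SIRS on admission. Time from onset does not appear in the list.

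**The concern.** The study asks whether timely TG reduction in early disease goes with a better course of organ failure. Two patients with the same Day 3 TG may be up to three days apart in their illness.

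That gap bears on both sides of the contrast. It bears on the exposure because it affects how far TG has already fallen and, if TG falls before entry, which patients are still above 11.3 mmol/L. It bears on the outcome because organ failure may be still to come, at its peak or resolving at entry, and a score that counts only the final failure-free stretch depends on which. The new-onset endpoint is exposed in the same way: one episode can count as new in an early entrant and as already present in a late one.

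If late entrants reach 5.65 mmol/L more or less often than early ones, the primary comparison partly compares stages of illness. An unadjusted rank test cannot separate the two.

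**Working it through.** **1. The plan's own figure.** The Sample Size Justification gives 87% power for 2 days (SD 5) and 82.5% for 1.5 days (SD 4) with 240 patients. Assume two-sided alpha 0.05 and 120 per group; neither is stated.

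- 2 / (5 × √(2/120)) = 3.098; power ≈ Φ(3.098 − 1.960) = 87.3%.
- 1.5 / (4 × √(2/120)) = 2.905; power ≈ Φ(2.905 − 1.960) = 82.8%.

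The noncentral t version gives 87.0% and 82.5%. The figures reproduce and are not in dispute.

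**2. Disease time at Day 3.** Under the Statistical Analysis numbering, Day 3 is about 48 h after enrolment.

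- Enrolled at onset: 0 + 48 = 48 h after onset.
- Enrolled at 72 h: 72 + 48 = 120 h after onset.

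The 14-day outcome window likewise ends about 14 to 17 days after onset. Table 1 numbers days differently ("Day0 is defined as the day from enrollment to 8 am the next day"), so its Day 2 is the analysis section's Day 3.

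**3. Who is still eligible later (illustration).** The document gives no TG trajectories. Assume TG falls exponentially from T0 at onset with half-life h.

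Time to reach 11.3 mmol/L = h × log2(T0/11.3). For an assumed T0 of 30, log2(30/11.3) = 1.409:

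- h = 24 h: 33.8 h.
- h = 48 h: 67.6 h.

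The faster decliner is eligible for half as long. Equivalently, entry at time t requires h > t × ln 2 / ln(T0/11.3):

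| Entry at | T0 = 20 | T0 = 30 |
|---|---|---|
| 12 h | 14.6 h | 8.5 h |
| 24 h | 29.1 h | 17.0 h |
| 48 h | 58.3 h | 34.1 h |
| 72 h | 87.4 h | 51.1 h |

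The onset TG needed for entry at 72 h is 11.3 × 2^3 = 90.4 mmol/L (h = 24) or 11.3 × 2^1.5 = 32.0 mmol/L (h = 48).

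**4. Link to the exposure (illustration).** Simulation with T0 lognormal (median 25 mmol/L, log-SD 0.5), an independent lognormal half-life (log-SD 0.5), and the same rate of fall before and after entry. Share of eligible patients below 5.65 mmol/L 48 h after entry:

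| Median half-life | Entry 12 h | 24 h | 48 h | 72 h |
|---|---|---|---|---|
| 18 h | 70% | 66% | 51% | 31% |
| 24 h | 52% | 50% | 37% | 21% |
| 36 h | 27% | 27% | 20% | 10% |

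Between 12 h and 24 h the share barely changes. Most of the fall comes with entry at 48 h or later.

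**5. Why this gives no bias in days.** With two entry strata, the confounding part of a difference in means is roughly (difference between exposure groups in the proportion of late entrants) × (difference in mean organ-failure-free days between late and early entrants). The document supplies neither factor, and the sign of the second is not known in advance.

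**The case against.** **Eligibility and follow-up start together.** A reader might call this left truncation, or say that fast decliners drop out. The document does not support either. Follow-up is not counted from onset with delayed entry ignored. A patient already at or below 11.3 mmol/L is outside the defined population and is not lost from it. The Discussion cites a guideline that recommends TG-lowering therapy above that level, so the criterion is coherent. On its own, selection before entry mainly limits generalisability. This stands.

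**A fall before enrolment is not documented.** Fasting is listed among the treatment modalities, and a reader might infer that it precedes entry. The text says only that eligibility is assessed after admission; it gives no gap between admission and enrolment. This stands too, so the enrichment for slow decliners is conditional. The 48 to 120 h spread does not depend on it.

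**This is one confounder among several, and an article condenses.** Severity and enrolment TG are also unadjusted in the primary test. Onset time must be established for eligibility, so its absence from the baseline list does not show that it is unrecorded. Nor is it shown to be excluded from the propensity score. These points are fair. However, the article does state the primary test and the rule for the secondary models, and neither secures adjustment for onset time. Enrolment TG is no substitute: the same value early and late in the window implies a different prior decline. SOFA is listed on admission, which need not coincide with enrolment.

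**Conclusion.** The point holds as confounding by disease stage at entry. From the stated rules alone, Day 3 can span about 48 to 120 h after onset, and the primary comparison as written does nothing about it. Adjustment in the secondary models depends on a significance test between groups, which is a poor way to choose a confounder.

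Size and direction cannot be computed from the document. The half-lives and onset TG levels used above are assumptions. They show a plausible link between entry time and reaching 5.65 mmol/L; they do not measure a shift in organ-failure-free days. The 72 h cap bounds the problem, and it is small if most patients enrol early. The entry criteria and the sample size are not in question. The change is worth making because the key variable must already be known for eligibility.

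**What to change.** Use hours from pain onset to enrolment as a prespecified term, whether or not it differs between groups:

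- **Primary comparison:** for example, a van Elteren rank test stratified by ≤24, >24–48 and >48–72 h, or a regression adjusting for onset time together with enrolment TG and baseline severity.
- **Other analyses:** include it in the Fine and Gray model, the secondary-outcome GLMs and the propensity score.
- **Sensitivity analysis:** restrict to patients enrolled within 24 h of onset.

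Recording the first TG since onset and any TG-lowering treatment before enrolment is optional, where charts allow.

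**Cost.** No extra patients. The primary test changes from a plain rank-sum test to a stratified or adjusted one, since a rank-sum test takes no continuous covariate. Recruitment began in November 2020 and the article appeared in December 2021, so onset times may have to be retrieved from screening records for patients already enrolled. The restricted analysis will be less precise. The optional items need chart abstraction.
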